Most stroke services have found considerable challenges in reducing iv rtPA treatment delays in hospital (i.e. door to needle time: DTNT), particularly, rapid access to brain imaging (i.e. door to scan time: DTST). Brain imaging is a vital component of assessment to exclude haemorrhagic stroke and patients with established ischaemic changes where thrombolysis would be futile. International clinical guidelines state that brain imaging should be performed immediately when a patient with thrombolysis potential arrives[7, 8]. An urgent scan is also indicated for other patients presenting with stroke symptoms including those taking anticoagulation medication and when a haemorrhage is suspected. Urgent treatments for these patients can include reversal of anticoagulation, intravenous medication to lower high blood pressure and possible neurosurgical intervention. Although across the NHS brain imaging was achieved within 1 hour for 43% of stroke admissions in 2014 there was wide variation between services and the low thrombolysis rate suggests that patients with the most to gain from rapid radiological assessment were not actively being selected[5]. An improvement in the early identification of patients who meet the criteria for an urgent scan could lead to a cost-effective reduction in dependency, mainly through an increase in the speed of iv rtPA treatment but also by improving access to other treatments and organised stroke care.

To date, most service interventions to reduce DTST and DTNT have focussed upon responses after patient admission to the Emergency Department (ED) or Acute Stroke Unit (ASU). Where improvements have been seen this usually reflects highly resourced centres, but even these may rely upon initial patient assessment by nursing and junior medical staff at nights and weekends. In some settings, the standard approach is remote stroke specialist assessment by video-link or telephone, increasing the reliance upon non-specialist staff for rapid and accurate information collection and communication at the bedside.

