#### Day 1 post-admission data:

Demographic information (age; gender; pre-stroke mRS)  
Date/time of hospital admission  
First blood pressure reading on admission  
First blood glucose reading on admission (capillary or serum glucose)  
Stroke severity on admission (National Institute of Health Stroke Score)  
Stroke onset or last known to be well time (stroke team judgement)  
Current use of anticoagulant medication  
Previous medical history (stroke; TIA; heart failure; atrial fibrillation; diabetes; hypertension)  
Hospital admission locations (ED; stroke unit; critical care; medical admissions ward, other ward)  
First brain imaging time, modality and result (CT / MRI; infarction/primary intracerebral haemorrhage)  
Thrombolysis treatment decision (yes / no; reason why thrombolysis not administered)  
Date/time of thrombolysis (if received)  
Use of other treatments (reversal of anticoagulation if haemorrhagic stroke; acute blood pressure lowering if haemorrhagic stroke or before intravenous thrombolysis; referral or transfer to neurosurgery; referral or transfer for intra-arterial treatment; use of intra-arterial treatments (yes / no; time of puncture)).  
Entry into another clinical trial on day 1 after admission (yes / no; which one)  
Date and time of admission to first stroke unit  
Date and time of assessment of swallow safety at first hospital

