*Estimation of consequences for resource use of an enhanced paramedic roles resulting from improved stroke outcomes:*

Data on the use of NHS inpatient resources used will be collected for patients in both arms of the trial. This data will be comprised of brain imaging modality, provision of thrombolysis and length of stay in hospital. In addition, data about community rehabilitation therapy, social service involvement and non elective episodes of secondary care post discharge will also be collected. This information will be collected as part of the study day 1/2 and day 90 data collection points.

Unit costs will be derived from routine sources for NHS and social care. The costs of providing the PASTA pathway for stroke mimic patients will be included within the economic evaluations but also presented separately. This will represent an economic worst case scenario because costs will be added but it will be assumed that there is no benefit (or harm) to these individuals. If the intervention still appears cost-effective in this scenario then the trial conclusions would be strengthened.

*Missing resource use data:*

Where there is data missing about post acute resource usage, essential items will be imputed from data present in the study for similar patients as defined by age, stroke severity and 3 month outcome[33]. Sensitivity analysis will quantify the degree of bias introduced by imputation.

*Sensitivity Analyses:*

Sensitivity analyses will be conducted on key parameters and assumptions contributing the estimates of cost-effectiveness. They will be designed to estimate the robustness of the findings and to provide additional information to decision makers. For example, how estimated cost-effectiveness is affected by assumptions about the extent of the resource and financial burden on ambulance services that result from paramedics performing an enhanced role.

*Long-term economic evaluation:*

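### The inpatient cost list in Protocol section 20 leaves out acute treatments that the day 1 form records, so the incremental cost is biased if the pathway changes their use

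*Protocol*

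**What the plan says.** Protocol section 20 (Economic analysis), in the part on the resource consequences of the enhanced role, describes the NHS inpatient data for both arms: "This data will be comprised of brain imaging modality, provision of thrombolysis and length of stay in hospital". It then adds that "data about community rehabilitation therapy, social service involvement and non elective episodes of secondary care post discharge will also be collected". These additions are community, social care and post-discharge items. None is a procedure or drug given during the index admission. Unit costs are to come from routine NHS and social care sources.

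Section 13 (Day 1 post-admission data) records more. The entry begins "Use of other treatments (reversal of anticoagulation if haemorrhagic stroke", continues with acute blood pressure lowering (in haemorrhagic stroke, or ahead of thrombolysis), then "referral or transfer to neurosurgery; referral or transfer for intra-arterial treatment", and ends with "use of intra-arterial treatments (yes / no; time of puncture".

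Section 5 (Background) says that better early identification of patients who need an urgent scan could reduce dependency, "mainly through an increase in the speed of iv rtPA treatment but also by improving access to other treatments and organised stroke care". The other urgent treatments named there are anticoagulant reversal, blood pressure lowering and possible neurosurgery. Intra-arterial treatment is not among them.

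The primary economic result is the cost per additional patient thrombolysed. A cost per QALY is reported as well.

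**The concern.** The sentence in section 20 names three items and contains no phrase such as 'including' or 'for example'. Applied as written, a participant who has an intra-arterial procedure gets the same inpatient cost as one with the same scan, thrombolysis status and length of stay who did not. Length of stay picks up any bed-days that these treatments add or save, but not the procedure or the drug.

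The protocol expects such treatments to occur. Section 12 foresees transfers to a neuroscience centre, and the day 2 data in section 13 cover outcomes after intra-arterial treatment. It also gives a reason why some of them might differ between arms: the pathway prompts paramedics to ask about anticoagulants (section 10.1), and section 5 mentions access to other treatments.

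The cost difference is the numerator of both economic ratios, so a true difference in use would carry straight into them. The bootstrap and the probabilistic analysis work on the costs that are in the model. They would not reveal an item that was never entered.

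**Working it through.** The plan states no cost figure on this point, so there is none to reproduce. The check has two parts.

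**1. Recorded items set against costed items (index admission)**

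| Item | Recorded in section 13 | Named for costing in section 20 |
|---|---|---|
| Brain imaging modality | yes | yes |
| Thrombolysis | yes | yes |
| Length of stay | yes (admission and discharge dates) | yes |
| Intra-arterial treatment | yes: use, and time of puncture | no |
| Referral or transfer for intra-arterial treatment | yes | no |
| Referral or transfer to neurosurgery | yes | no |
| Neurosurgical operation | no | no |
| Anticoagulant reversal | yes, if haemorrhagic stroke | no |
| Acute blood pressure lowering | yes, if haemorrhagic stroke or before thrombolysis | no |

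The rest of section 20 (missing resource data, sensitivity analyses, long-term model, uncertainty) does not add any of the lower six rows.

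**2. Size of the omission**

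Inputs from the protocol: a postulated thrombolysis gain of 0.53 − 0.43 = 0.10, and 856 control and 428 intervention participants analysable (section 18, Sample size). Inputs assumed, because the protocol gives none: the difference in use between arms, and the unit cost beyond bed-days.

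- Cost omitted per participant = difference in use × unit cost.
- Effect on the cost per additional patient thrombolysed = cost omitted per participant / 0.10.

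For a true 1-point difference in use:

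- at £5,000: 0.01 × 5,000 = £50 per participant, and 50 / 0.10 = £500 per additional patient thrombolysed;
- at £10,000: 0.01 × 10,000 = £100 per participant, and 100 / 0.10 = £1,000.

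Under wider assumptions:

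- 0.5 points at £2,000: 0.005 × 2,000 = £10 per participant, or £100 per additional patient thrombolysed;
- 3 points at £15,000: 0.03 × 15,000 = £450 per participant, or £4,500 per additional patient thrombolysed;
- no difference in use: zero at any unit cost.

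The sign follows the direction of the difference. Higher use in the intervention arm means that the incremental cost is understated, and lower use means that it is overstated.

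**Chance imbalance, for comparison.** The standard error of a difference in use is √[p(1−p)(1/856 + 1/428)]. For assumed p of 1%, 3% and 5% this is 0.59, 1.01 and 1.29 percentage points. The protocol's design effect, 1 + (5 − 1) × 0.02 = 1.08, raises these by about 4%, since √1.08 = 1.04. One standard error is therefore worth 0.0059 × 5,000 ≈ £29 to 0.0129 × 10,000 = £129 per participant. This is sampling variation around zero, not bias.

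**The case against.** The strongest reply is that the sentence describes data to be collected and is not a rule on what is costed. Section 13 collects more than the three items, and the unit-cost sentence is not restricted to them. Where the protocol means to exclude a cost, as with producing the training material, it says so. A later health economics plan could itemise the costs, and the planned sensitivity analyses are open-ended. This carries some weight: the omission is not declared as an exclusion. It does not settle the matter, because the list stands under the heading on estimating resource use and nowhere does the protocol say that the other treatments will be costed.

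Several stronger readings are tempting and are not supported:

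- A reader might infer that the protocol expects the pathway to raise use of intra-arterial treatment. Section 5 says only that there could be better access to other treatments, and it does not name that one.
- A reader might infer that the cost difference is wrong whenever use differs. Differences in separate items can offset each other, and bed-days are already counted.
- A reader might infer that the evaluation counts the benefits of these treatments without their cost. That is true at most in part. The primary ratio has patients thrombolysed as its denominator. The 90-day health model is driven by thrombolysis, time since onset, and physiological and demographic factors. Observed 90-day mRS scores are also to be used for QALYs, so some consequences may enter there.
- A reader might take the chance-imbalance figures as bias. If true use is equal, leaving the items out does not shift the expected cost difference, and putting them in adds variance.
- A reader might assume that neurosurgery is already recorded. Only referral or transfer is.

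**Conclusion.** The point stands in limited form. Section 20 restricts index-admission resource use to three items although section 13 records further acute treatments, and followed as written it omits their procedure and drug costs beyond bed-days. The incremental cost is then biased if the pathway changes how often they are used. The protocol makes such a change plausible for anticoagulant reversal, blood pressure lowering and neurosurgery, but does not establish it for any treatment.

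The size cannot be derived from the documents. The working figure of £500 to £1,000 per additional patient thrombolysed, for each true 1-point difference, depends on the assumed unit cost and on the 10-point gain being achieved. A smaller gain would enlarge it, and a cheaper treatment would shrink it in proportion. The primary clinical analysis is not affected.

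**What to change.** In section 20, extend the inpatient list to the treatments already recorded on day 1: intra-arterial treatment, referral or transfer for it or to neurosurgery, anticoagulant reversal, and acute blood pressure lowering. Take the unit costs from the routine sources already named. Report the incremental cost with and without these items as a sensitivity analysis. Cost the neurosurgical operation itself only if it can be identified from existing records, since the day 1 form does not capture it. Referral and transfer are listed together, so check whether the form separates them before assigning a transfer cost.

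The change takes one amended sentence and a few more unit costs, and needs no new data collection for the recorded items. Its drawback is that rare, costly items will slightly widen the confidence interval for cost.

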#### *Quantifying uncertainty in estimates of cost effectiveness:*

Bootstrapping will provide estimates of the imprecision surrounding estimates of costs and incremental cost per unit of outcome. Results will be presented as cost effectiveness acceptability curves (CEACS)[32]. Probabilistic sensitivity analyses will be carried out on key cost parameters. If after initial analysis it is found that the cost-effectiveness of the intervention is sensitive to one or more inputs, an Expected Value of Perfect Parameter Information (EVPPi) will be undertaken focusing on those inputs[35].

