## 20. Economic analysis

The primary economic analysis will be a within trial economic evaluation to estimate cost-effectiveness of the enhanced role versus usual care in increasing the proportion of patients receiving intravenous thrombolysis, and will report a cost per additional patient thrombolysed. In addition a cost utility analysis will be conducted to estimate cost per quality adjusted life years (QALYs).

To derive health outcomes at 90 days, a model based simulation will be constructed using a model previously developed which describes outcomes at 90 days based on whether or not thrombolysis was given, time elapsed since stroke onset if it was given and other physiological and demographic factors[29]. A Monte Carlo approach will be taken in which different subsets of trial participants from each arm are repeatedly sampled and their health status at 90 days is estimated. The effectiveness and cost-effectiveness of the enhanced role versus usual care will be the average of all the samples, together with an estimate of uncertainty.

Pre-stroke and 90 days mRS scores will be used to estimate QALYs using mapping algorithm which has been developed by Rivero-Arias et al. to estimate the EQ5D scores from mRS values[30]. Mortality and utility values will be converted into QALYs using the area under the curve method, controlling for baseline health utility derived from mRS[31]. The uncertainty analysis results will be presented as a cost effectiveness acceptability curve (CEAC)[32]. The CEAC will show the probability that an enhanced role is cost-effective

compared with usual care, given the observed data, for a range of maximum monetary values that decision makers may be prepared to pay for percentage change in proportion of patients that are thrombolysed /extra QALY.

*Estimating the resources used and costs of providing an enhanced paramedic role:*

The costs of paramedic time will be based on the equivalent hourly wage for the appropriate grades. The time taken to complete the training will be recorded by the computer based training software. Training material productions costs will be excluded from the evaluation. The times from the “on scene” to “handover” and “clear to respond to another incident” will be recorded and used to estimate additional ambulance service resource utilisation that may result from the enhanced paramedic role. The costs of these resources will be obtained from Ambulance Trusts and published sources including the PSSRU.

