In common with other economic evaluations, a further modelling analysis will be undertaken to extrapolate the results of the trial beyond the 90 days, which will help to inform likely longer-term cost and effects. The model will be a microsimulation state transition model made up of three states (independent, dependent and death) to which costs and QALYs will be attached[34]. To estimate the longer term effects of increased independence that may result from an enhanced paramedic role in the timely treatment of stroke, the economic model will describe changes in dependency status over time. Outcomes after subsequent strokes (dependency measured by the modified Rankin Score at day 90) will be estimated

using a published decision analytic model (DAM) which predicts the outcome of treating acute stroke with and without thrombolysis[29].

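### The probabilistic sensitivity analysis names cost inputs only, so the modelled QALY and long-term acceptability curves leave out uncertainty in effect, utility-mapping and transition inputs

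*Protocol*

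**What the plan says.** Section 20 sets out three layers of economic result.

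- **Primary:** a within-trial cost per additional patient thrombolysed.
- **90-day cost-utility analysis:** for health at 90 days, "a model based simulation will be constructed using a model previously developed which describes outcomes at 90 days". QALYs come from pre-stroke and 90-day mRS through a published mapping to EQ-5D.
- **Long-term extrapolation:** a three-state microsimulation (independent, dependent, dead) with costs and QALYs attached to the states. Outcomes after later strokes come from a published decision model.

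Uncertainty is handled as follows.

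- In the 90-day simulation, "A Monte Carlo approach will be taken in which different subsets of trial participants from each arm are repeatedly sampled". The result "will be the average of all the samples, together with an estimate of uncertainty".
- Under the heading on quantifying uncertainty, "Bootstrapping will provide estimates of the imprecision surrounding estimates of costs and incremental cost per unit of outcome". These results are shown as acceptability curves.
- The same paragraph continues: "Probabilistic sensitivity analyses will be carried out on key cost parameters".
- If cost-effectiveness proves sensitive to any inputs, "an Expected Value of Perfect Parameter Information (EVPPi) will be undertaken focusing on those inputs".
- Under Sensitivity Analyses, key parameters and assumptions are to be varied, without limitation to costs and without saying that this will be probabilistic.

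The purpose of the curve is also stated: "The CEAC will show the probability that an enhanced role is cost-effective".

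**The concern.** The QALY and long-term results rest on quantities that were estimated outside the trial. These are the effect of thrombolysis and its timing on 90-day health, the conversion of mRS to utility, and movement between states over time. Resampling trial participants carries sampling error in thrombolysis rates, treatment times and observed costs. It cannot carry estimation error in coefficients taken from other sources, because every replicate passes through the same coefficients. A probabilistic analysis confined to costs does not supply the missing part.

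The curve would then show the probability of cost-effectiveness on condition that those inputs equal their point estimates. That is narrower than the probability the section says it will show, and a decision maker would read the curve as firmer than it is.

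The planned value-of-information step has a related difficulty. Expected value of perfect parameter information for an input requires a probability distribution for that input. The stated probabilistic analysis provides distributions for cost inputs but not for effect inputs.

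**Working it through.** **1. What varies in each draw of the acceptability curve, as written**

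| Input | Varied by | Enters the curve? |
|---|---|---|
| Thrombolysis rates, treatment times, observed costs, observed mRS | Bootstrap; participant resampling | Yes |
| Key cost parameters | Probabilistic sensitivity analysis | Yes |
| Decision-model effect and time coefficients | No probabilistic step stated | No |
| mRS-to-EQ-5D mapping coefficients | No probabilistic step stated | No |
| Transition probabilities and state utilities | No probabilistic step stated | No |

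The general sensitivity analyses may vary the last three rows. One-way or scenario analyses are reported beside an acceptability curve and do not enter it.

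**2. Illustration of size**

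The protocol gives no figure for the uncertainty of cost-effectiveness, so there is none to reproduce.

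Inputs from Section 18, Sample size: thrombolysis proportions 0.43 and 0.53; analysable numbers 856 control and 428 intervention; average cluster size 5; intra-cluster correlation 0.02.

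Inputs assumed, because the documents give none:

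- CV: the coefficient of variation of the modelled health gain per extra patient thrombolysed.
- k: the standard deviation of the cost difference on the net-benefit scale, as a multiple of the standard error of the thrombolysis difference.

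Design effect: 1 + (5 − 1) × 0.02 = 1.08.

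Variance of the difference: v = 1.08 × (0.43 × 0.57/856 + 0.53 × 0.47/428) = 1.08 × (0.0002863 + 0.0005820) = 0.000938. The standard error is √v = 0.0306.

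Scale the mean gain per extra patient thrombolysed to 1. Net benefit is then difference × gain − cost, with the three parts taken as independent.

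- Variance reported with the gain fixed: v(1 + k²).
- Variance with the gain uncertain: v(1 + CV²) + 0.10² × CV² + k²v.

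R is the square root of the second divided by the first. With no cost uncertainty (k = 0):

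- CV 0.2: (0.000938 × 1.04 + 0.01 × 0.04)/0.000938 = 0.001375/0.000938 = 1.47, so R = 1.21.
- CV 0.5: (0.000938 × 1.25 + 0.01 × 0.25)/0.000938 = 0.003672/0.000938 = 3.92, so R = 1.98.

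With net benefit taken as approximately normal, a reported probability of 0.95 becomes Φ(1.645/R). Each cell shows R and that probability.

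| CV | k = 0 | k = 1 | k = 2 | k = 3 |
|---|---|---|---|---|
| 0.1 | 1.06; 0.940 | 1.03; 0.945 | 1.01; 0.948 | 1.01; 0.949 |
| 0.2 | 1.21; 0.913 | 1.11; 0.931 | 1.05; 0.942 | 1.02; 0.946 |
| 0.3 | 1.43; 0.875 | 1.24; 0.909 | 1.10; 0.933 | 1.05; 0.941 |
| 0.5 | 1.98; 0.797 | 1.57; 0.853 | 1.26; 0.904 | 1.14; 0.926 |

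For each CV, the k = 0 column is the upper bound on R. The plan does propagate cost uncertainty, so the true position lies to the right of that column by an unknown amount. Probabilities below 0.5 move upwards by the same rule, so the error is always away from 0.5.

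**The case against.** Five points deserve weight.

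- **The general sensitivity analyses are not limited to costs.** A reader might infer from the cost-only sentence that the whole economic evaluation treats the modelled effect as known exactly. The documents do not support that, because effect inputs may be varied under Sensitivity Analyses. What remains is that nothing makes that variation probabilistic, so it does not reach the curves.
- **The value-of-information step refers to inputs in general.** A reader might infer that it could only ever identify cost inputs. The text does not say so. Planning it for any sensitive input implies that a distribution would be found. What stands is that two adjacent sentences do not fit together: the step needs distributions that the probabilistic analysis, as described, does not supply for effect inputs.
- **Observed 90-day mRS may feed the 90-day QALYs.** Section 20 describes both a modelled route to 90-day health and the use of 90-day mRS scores, and does not say which drives the curve. If observed scores are used, the bootstrap carries the health-effect uncertainty and only the mapping stays fixed. This narrows the point at 90 days. It leaves the extrapolation untouched.
- **The size may be small.** With a CV of 0.1, or with large cost uncertainty, the table shows hardly any change. This stands.
- **Detail may sit in an analysis plan that is not shown.** That would answer a complaint about missing detail. Here, however, the protocol states a scope, and an analysis plan that followed it would be cost-only.

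**Conclusion.** The point holds for the long-term cost-per-QALY curve, and for the 90-day curve to the extent that it uses the decision model or the mapping. As written, both would understate uncertainty, with probabilities too far from 0.5. The direction follows from the text. The size does not, because the documents give neither the precision of the external inputs nor that of the cost difference.

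On the assumptions above, the standard deviation of net benefit would be at most about 1.2 times (CV 0.2) to 2.0 times (CV 0.5) the one reported. Cost uncertainty pulls the ratio towards 1. A reader might infer that a reported 95% would conceal far wider uncertainty; that is not established. In the illustration 0.95 becomes anything from 0.949 to 0.797, depending on the assumed CV and k.

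The primary economic result, cost per additional patient thrombolysed, uses no modelled health effect and is not affected. This is a worthwhile correction to the secondary economic analyses and does not threaten the trial's main conclusions.

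**What to change.** In Section 20, under the heading on quantifying uncertainty, widen the scope of the probabilistic sensitivity analysis from key cost parameters to all uncertain model inputs: the effect and time coefficients of the decision model, the mapping coefficients, the transition probabilities, the state utilities and the costs. Draw these jointly, one draw with each bootstrap replicate. Build the modelled QALY and long-term acceptability curves, and the value-of-information analysis, from those draws.

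The cost is a short wording change and some extra programming. Standard errors will have to be assumed where a source gives none, and those assumptions should be reported. The curves will be flatter. No new data and no change to trial conduct are needed.
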